### 12.8 PHARMACOKINETIC (PK) ANALYSIS SET

The PK analysis set includes all subjects in the safety who received at least 1 dose of nafithromycin and had at least 1 analyzable plasma PK sample.

[figure not shown]

**13. DISPOSITION**

A clear accounting of the disposition of all subjects who enter the study will be provided, from screening to study completion.

Number and percentage of subjects who were screened, screen failed (including reasons for screen failures) will be summarized. For Enrolled subjects, the number randomised, completed study drug, completed through Day 4, EOT and TOC, completed the study and reasons for discontinuations of study drug as well as discontinuation from study will be summarized by treatment group and overall. This will be repeated using the MITT analyses set.

The number and percentage of subjects enrolled at each investigational site will also be presented by treatment and overall for all enrolled subjects.

Number and percentage of subjects in each analyses set, including reasons for exclusions, will also be presented by treatment and overall for all enrolled subjects.

The number of subjects with MTBC detected will be summarized by treatment group in the ITT analyses set.

[figure not shown]

#### 14. PROTOCOL DEVIATION

Protocol deviations (PDs) will be classified as significant (S) or non-significant (NS). All deviations will be listed. Significant PDs will be summarized by treatment group in the ITT and MITT analyses set.

The list of categories for the PD is shown below along with the abbreviated description to be used in summaries and listings.

**Table 1. Definitions of Significant and Non-Significant Protocol Deviations**

| No.                           | Deviation Description                                                                                                                                                                                                                                        | Abbreviated Description                                           |
|-------------------------------|--------------------------------------------------------------------------------------------------------------------------------------------------------------------------------------------------------------------------------------------------------------|-------------------------------------------------------------------|
| Significant Deviations |                                                                                                                                                                                                                                                              |                                                                   |
| 1                             | Subject was included in the study who did not meet eligibility criteria                                                                                                                                                                                      | Eligibility Criteria not met                                      |
| 2                             | Any randomization to the wrong stratum                                                                                                                                                                                                                       | Randomization within incorrect PORT risk class                    |
| 3                             | Subject who received study medication other than the one to which she/he was assigned                                                                                                                                                                        | Treatment opposite randomized assignment                          |
| 4                             | Subject who was dosed incorrectly, had large departures from dosing schedule or was otherwise non-compliant with study drug                                                                                                                                  | Incorrect dosing or non-compliance with study drug administration |
| 5                             | Subject who was dosed more than 7 days                                                                                                                                                                                                                       | Received > 7 days of study drug                                   |
| 6                             | Subject who received a non-study systemic antibacterial agent with potential activity against CABP pathogens                                                                                                                                                 | Received prohibited systemic antimicrobial                        |
| 7                             | Subject who received another prohibited medication as defined in the protocol                                                                                                                                                                                | Received other prohibited medications (non-antimicrobial)         |
| 8                             | PDs that impact efficacy assessments and are directly related to the study endpoints such as delayed or missed or assessments done outside of the protocol-defined windows at Day 4, EOT and TOC visits, deviations on the IP management and administration. | Missed, incomplete or non-adherence to efficacy assessments       |
| 9                             | Deviations relating to informed consent document administration. (e.g. Study specific procedure performed prior to obtaining Informed Consent, Subject signed incorrect ICF version, and subject did not sign the most recent version of the ICF at          | Informed consent deviation                                        |

[figure not shown]

|                            |                                                                                                                                                                                                                                                                                                                                                                                                                                     |                                                                |
|----------------------------|-------------------------------------------------------------------------------------------------------------------------------------------------------------------------------------------------------------------------------------------------------------------------------------------------------------------------------------------------------------------------------------------------------------------------------------|----------------------------------------------------------------|
|                            | the next available visit.)                                                                                                                                                                                                                                                                                                                                                                                                          |                                                                |
| Non-Significant Deviations |                                                                                                                                                                                                                                                                                                                                                                                                                                     |                                                                |
| 1                          | AE reporting (specifically PDs that do not compromise the safety of the subjects)                                                                                                                                                                                                                                                                                                                                                   | Missed AE report where safety was not compromised              |
| 2                          | Study procedures not impacting the evaluation of efficacy or safety of the study participants (e.g. Any assessment/laboratory procedures not conducted as per protocol, or not required for reasons relevant to patient safety such as samples sent for central laboratory analysis for FU Day 31 although there was no clinically significant laboratory abnormalities noted at or after the TOC Visit- as mentioned in the time). | Procedure not impacting efficacy or safety assessment not done |
| 3                          | Investigational product (includes minor occasional deviations from the scheduled times of administration that is q24h ( $\pm$ 4 h) between Day 1 and EOT, with the exception of Day 2 in which an additional window of 4 h may be utilised, depending on the randomisation time on Day 1).                                                                                                                                          | Minor deviations from dosing schedule                          |

Note that criteria for the CE analyses set are a subset of the protocol deviations listed above. In the protocol these were referred to as ‘violations’.

[figure not shown]

## **15. BASELINE CHARACTERISTICS**

### **15.1 Demographics and Baseline Characteristics**

Demographics and baseline characteristics such as gender, age, race, ethnicity, weight, and body mass index (BMI), PORT scores, relevant medical history, and clinical signs and symptoms will be summarized by treatment group for the MITT and Safety analyses set.

Vital signs at baseline will be summarized in the MITT analyses set.

### **15.2 Medical History, Co-Morbid Conditions and Markers of CABP**

Medical/Surgical history will be summarized for the Safety analyses set by treatment group and overall. Descriptive summaries of Co-morbid conditions, Markers of CABP and vital signs will be generated by treatment group in the MITT analyses set. See mock shells for the specific list of parameters included.

### **15.3 Gram Stain and Microbiological Results at Baseline**

Gram stain results of (induced and/or expectorated) sputum samples as well as BAL and thoracentesis (if present) at baseline will be summarized using frequency and percentage by treatment group for the MITT analyses set.

Identification of typical pathogenic organisms at baseline from respiratory or blood specimens or urinary antigen tests will be summarized by the treatment group for the expanded mMITT and mMITT analyses set.

Pathogenic organisms identified at baseline from serology testing and urinary antigen tests will be summarized by treatment group for the expanded mMITT and the mMITT analysis set.

Infections by Gram type and number of pathogens isolated at baseline from respiratory or blood specimens, serology or urinary antigen tests will be summarized by treatment group for expanded mMITT and mMITT analyses set. The number of subjects with infections due to: monomicrobial Gram-positive, monomicrobial Gram-negative (including subjects with fastidious, or non-fastidious organisms), monomicrobial any Gram-positive or negative, monomicrobial atypical, all monomicrobial, polymicrobial all, polymicrobial Gram-positive, polymicrobial Gram-negative, polymicrobial typical pathogens only, (with the same Gram type), polymicrobial typical and atypical, where the subject has a single typical organism or the same Gram type, if more than one typical), mixed Gram-negative and Gram-positive: overall as well without atypical pathogens will be tabulated. A tabulation of the number of pathogens (1, 2,  $\geq 3$ ) identified per subject will be included.

Descriptive statistics of minimum inhibitory concentration (MIC) results at baseline of nafithromycin and also of moxifloxacin in the mMITT analyses set will be provided including the number isolated and number tested, minimum, maximum, MIC50 and MIC90. Here MIC50 and MIC90 are the 50th and the 90th percentile values of MIC obtained rounded to the nearest whole value.

[figure not shown]

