| GCP      | Good Clinical Practice                                                    |
| HIV      | Human Immunodeficiency Virus                                              |
| ICF      | Informed Consent Form                                                     |
| ICH      | International Council for Harmonisation                                   |
| INR      | International Normalized Ratio                                            |

[figure not shown]

|                   |                                                     |
|-------------------|-----------------------------------------------------|
| IP                | Investigational Product                             |
| ITT               | Intent-to-Treat                                     |
| IXRS              | Interactive Voice/Web Response System               |
| LDH               | Lactate Dehydrogenase                               |
| LLN               | Lower Limit of Normal                               |
| MCH               | Mean Corpuscular Hemoglobin                         |
| MCHC              | Mean Corpuscular Hemoglobin Concentration           |
| MCV               | Mean Corpuscular Volume                             |
| MDR               | Multi-Drug Resistant                                |
| MedDRA            | Medical Dictionary for Regulatory Activities        |
| MIC               | Minimum Inhibitory Concentration                    |
| MIC 50 | 50 th Percentile of the MIC Distribution |
| MIC 90 | 90 th Percentile of the MIC Distribution |
| MITT              | Modified Intent-to-Treat                            |
| mMITT             | Microbiological Modified Intent-to-Treat            |
| MTBC              | Mycobacterium Tuberculosis Complex                  |
| N/A               | Not Applicable                                      |
| NS                | Non-Significant                                     |
| PCS               | Potentially Clinically Significant                  |
| PN                | Preferred Name                                      |
| PDs               | Protocol Deviations                                 |
| PH                | Potential of Hydrogen                               |
| PK                | Pharmacokinetic(s)                                  |
| PO                | Orally, Per os or by Mouth                          |

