**Table 2. Secondary Analysis Variables by Visit and Analyses Set.**

| Analysis Variable                        | Visit       | Analyses set |       |             |
|------------------------------------------|-------------|--------------|-------|-------------|
|                                          |             | MITT         | mMITT | CE (at TOC) |
| Clinical Response                        | Day 4       | NA (primary) | X     | X           |
| Investigator-determined Clinical Outcome | EOT         | X            | X     | X           |
|                                          | TOC         | X            | X     | X           |
| Hospital re-admission Rates              | Prior to FU | X            |       |             |

Abbreviations: CE = Clinically Evaluable; MITT = Modified Intent-to-Treat; mMITT = Microbiological Modified Intent-to-Treat; TOC = Test of Cure

Similar tabulations will be done for the by-subject favourable clinical response at Day 4 and the by-subject investigator-determined clinical cure rate at TOC in subjects with bacteremia and in subjects with at least one multi-drug resistant (MDR) pathogen, defined as resistant to 2 or more antibiotics belonging to different classes (e.g., macrolides, beta-lactams, fluoroquinolones and tetracyclines) using both the US Food and Drug Administration Susceptibility Test Interpretive Criteria (FDA STIC) and the European Committee on Antimicrobial Susceptibility Testing (EUCAST) interpretive criteria and

[figure not shown]

identified from an appropriately collected respiratory specimen or blood in the mMITT analysis set, except that CIs will not be included if less than 10 subjects per treatment group are obtained.

The clinical response at day 4 as well as the investigator-determined clinical outcome at TOC will be summarized for the following subgroups in the mMITT analyses set:

- Subjects with any monomicrobial infection
- Subjects with monomicrobial infection caused by Gram-negative pathogens
- Subjects with monomicrobial infection caused by fastidious Gram-negative pathogens
- Subjects with monomicrobial infections caused by non-fastidious Gram-negative pathogens
- Subjects with monomicrobial infections caused by Gram-positive pathogens
- Subjects with monomicrobial infections caused by atypical pathogens
- Subjects with any polymicrobial infections [Note: subjects with both typical (single typical or of the same Gram type is  $> 1$ ) and atypical pathogen are included here]

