- Subjects with polymicrobial infections due to Gram-positive pathogens only
- Subjects with polymicrobial infections due to Gram-negative pathogens only
- Subjects with polymicrobial infections due to atypical pathogens only
- Subjects with polymicrobial infections due to typical pathogens only of the same Gram type
- Subjects with mixed Gram-positive and Gram-negative Infections
- Subjects with mixed Gram-positive and Gram-negative Infections without atypical pathogens

The by-pathogen favourable clinical response at Day 4 and also the by-pathogen clinical cure rate at TOC will be summarized in the mMITT analyses set.

In the by-pathogen summaries, typical pathogens will be categorized as Gram-negative-fastidious, Gram-negative non-fastidious and Gram-positive.

The by-pathogen favourable clinical response at Day 4 and also the by-pathogen cure rate at TOC will also be summarized in the mMITT analyses set for:

- Subjects with monomicrobial infections due to typical pathogens
- Subjects with monomicrobial infections due to atypical pathogens
- Subjects with polymicrobial infections
  - Subjects with polymicrobial infections due to typical pathogens only
  - Subjects with polymicrobial infections due to typical and atypical

[figure not shown]

pathogens

- Subjects with polymicrobial infections due to atypical pathogens only

The incidence of superinfections and new infections will be summarized and listings by pathogen will be provided for each treatment group. In addition, subjects in the mMITT analyses set, whose baseline pathogen(s) has a decreased susceptibility (defined as a 4-fold increase in the baseline MIC) to the study treatment received in a post-baseline culture will be listed.

An assessment of hospitalisation (defined as re-admission to the hospital if previously hospitalised on or after study drug initiation [Day 1] and before FU or initial hospital admission [if not previously hospitalised] for any reason between the initiation of the study drug (Day 1) and before FU will be summarized using frequency and percentage for subjects in MITT analyses set.

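### SAP section 15.3 rounds MIC50 and MIC90 to whole numbers, so any percentile below 0.5 would be reported as 0, which is not a possible MIC

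*SAP*

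**What the plan says.** SAP section 15.3 plans descriptive statistics for MIC "results at baseline of nafithromycin and also of moxifloxacin in the mMITT analyses set". The statistics are listed as "including the number isolated and number tested, minimum, maximum", followed by MIC50 and MIC90. The section then says how the last two are obtained: they are the 50th and 90th "percentile values of MIC obtained rounded to the nearest whole value".

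The rounding is attached to these two percentiles only. Nothing in the section rounds the minimum or maximum. The abbreviation list (SAP section 3) describes MIC50 and MIC90 each as a "Percentile of the MIC Distribution", with no mention of rounding. The SAP gives no MIC values, units or dilution range, does not name a percentile method, and does not explain what a whole value is.

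**The concern.** MICs are read on a two-fold dilution scale that continues below 1 (0.5, 0.25, 0.12, 0.06 and so on). Rounding to integers suits that scale badly, because all the steps below 0.5 merge into 0. A zero would mean that growth is inhibited with no drug present, so it is not a coarse value but an impossible one.

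What is at stake is the readability of one baseline table. MIC50 and MIC90 are its only summaries of where the bulk of the distribution lies; the rest are counts and extremes. If both drugs had percentiles below 0.5, the table would show 0 against 0 and say nothing about their relative activity.

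**Working it through.** The SAP states no MIC figure, so there is nothing to reproduce. The check applies the stated rule to assumed values.

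**Inputs.** From SAP section 15.3: the rounding rule for MIC50 and MIC90, and the absence of one for minimum and maximum. Assumed: a two-fold series from 0.008 to 8 in the unit the laboratory reports, and percentiles taken as observed values, that is, the smallest value at which the cumulative share of isolates reaches 50% or 90%.

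**Step 1: the rule on single values.** Reported value = nearest integer to the percentile.

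| Percentile | Ties rounded up | Ties rounded to even |
|---|---|---|
| 0.008, 0.015, 0.03, 0.06, 0.12, 0.25 | 0 | 0 |
| 0.5 | 1 | 0 |
| 1, 2, 4, 8 | unchanged | unchanged |

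The values that merge into 0 span 0.25 / 0.008 = 31.25, about a 31-fold range. At 0.5 the result depends on a tie rule that the SAP does not give.

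**Step 2: the rule on whole distributions.** Three invented sets of 100 isolates:

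- Low: 10 at 0.015, 20 at 0.03, 40 at 0.06, 25 at 0.12, 5 at 0.25. Cumulative counts 10, 30, 70, 95, 100.
- Middle: 10 at 0.06, 30 at 0.12, 40 at 0.25, 15 at 0.5, 5 at 1. Cumulative counts 10, 40, 80, 95, 100.
- High: 10 at 0.5, 40 at 1, 30 at 2, 20 at 4. Cumulative counts 10, 50, 80, 100.

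| Set | Minimum | Maximum | MIC50 / MIC90 unrounded | Under the SAP rule |
|---|---|---|---|---|
| Low | 0.015 | 0.25 | 0.06 / 0.12 | 0 / 0 |
| Middle | 0.06 | 1 | 0.25 / 0.5 | 0 / 1 (ties up) or 0 / 0 (ties to even) |
| High | 0.5 | 4 | 1 / 4 | 1 / 4 |

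**Step 3: consistency within the table.** The minimum is above 0 and cannot exceed any percentile. Whenever a percentile is reported as 0, it therefore lies below the minimum printed beside it, provided the minimum is shown as recorded. In the low set the row would read: minimum 0.015, MIC50 0, MIC90 0, maximum 0.25.

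**Step 4: percentile method.** If a method that averages neighbouring values were used, ten isolates split evenly between 1 and 2 would give 1.5, reported as 2, although 1 already inhibits half of them. This is only a possibility, since the SAP names no method.

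**The case against.** The strongest defence is that 'whole value' was meant as a real dilution step rather than an interpolated number, which would be sound practice. The text does not say so, and the whole-number reading is the natural one. If the dilution step was intended, the sentence still needs the same correction.

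The second defence is that the harm may never arise. The mMITT set (SAP section 12.6) mixes varied organisms, and nothing in the SAP shows where either drug's percentiles lie. That stands: the size of the effect is unknown, and the high set above shows no effect at all.

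A reader might infer three stronger things, none of which the SAP supports:

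- *That the susceptibility table as a whole is lost.* Only two statistics are rounded. The number isolated, number tested, minimum and maximum remain, and SAP section 11 promises subject listings of all source data, from which the percentiles can be recovered.
- *That the resistance outputs in SAP section 19.3 are compromised.* Decreased susceptibility is "defined as a 4-fold increase in the baseline MIC", comparing a subject's own baseline pathogen with a later culture. Multi-drug resistance is "defined as resistant to 2 or more antibiotics belonging to different classes", judged by published interpretive criteria. Neither uses MIC50 or MIC90.
- *That the efficacy conclusions in the mMITT set are weakened.* Those rest on clinical response and cure rates. No endpoint, hypothesis test or analysis-set definition uses these percentiles.

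**Conclusion.** The rule is wrong as written, and the point is minor. The SAP states an explicit derivation that reports any MIC50 or MIC90 below 0.5 as 0, an impossible value that contradicts the minimum in the same table, and it leaves the result at exactly 0.5 undefined.

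The effect runs from loss of both percentiles for a drug, if both lie below 0.5, to none, if they sit on whole-number dilutions of 1 or more. Where the trial falls in that range cannot be told from the SAP. The conclusion rests on reading 'whole value' as a whole number. The dilution series and the three isolate sets are illustrations, not trial data. The consequence stays within one descriptive baseline output.

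**What to change.** Replace the last sentence of SAP section 15.3 with: *MIC50 and MIC90 are the lowest tested concentrations at which at least 50% and 90% of isolates are inhibited, reported at the tested concentration without rounding to whole numbers.*

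This removes the zeros, settles the case of exactly 0.5, and fixes the percentile method. In the illustrations it gives 0.06 / 0.12, 0.25 / 0.5 and 1 / 4.

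The cost is one sentence in the SAP and a small change to one table program. Design, data collection and every other planned analysis stay as they are.
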